### Study design

The study will be implemented over 12-months as a two-group (intervention; waitlist control) quasi-experimental trial using a staggered cohort design (Table 1). At each of three time periods, separated by 10 weeks, a cohort of 20 families will be recruited. Each cohort will be divided into an intervention and waitlist control group (10 families in each). Consequently, a total of 60 families (30 in the intervention group and 30 in the waitlist control group) will be enrolled. Upon confirmation of study eligibility, a baseline data collection appointment will be scheduled at the participating family’s home or the community center during the two weeks preceding intervention commencement. Data will be collected on the primary food preparing caregiver and all children 4–10 years old. Written caregiver consent and child assent will be obtained. Data will be collected on all outcomes via direct measure and questionnaires at baseline (time point 0, T0), 10-week post-test (time point 1, T1), and 10-week follow-up (time point 2, T2). Repeatability of the intervention (replication) will be evaluated by assessing measures on the waitlist control group at T1 and T2. Assessments will last up to 90 min. A team of trained research staff, blinded from group assignment, will facilitate data collection. Caregiver participants will receive a $25 grocery store gift card at each data collection point for their participation in the research. All study materials and procedures have been approved by the Institutional Review Board at Ohio State University.

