**Table 1 Tab1:**
[figure not shown]
Simple Suppers Intervention Study Design: Two-Group, Staggered Cohort Quasi-Experimental Design

Following baseline data collection, families will decide whether to enroll in either the upcoming 10-week session of Simple Suppers (intervention group) or to wait for 10-weeks (waitlist control group) after which time they would begin the Simple Suppers program. Randomization of families is not feasible because of scheduling conflicts with participating families, the desire of families to participate in the program with families they know, and the need to establish trust with the site/participating families; thus, to preserve sample size and establish trust with the site/participating families, the personal preference of participating families will determine group membership.

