### Sample size and data analysis

Sample size was determined by examining the power of the test for comparing increases in frequency of family meals (day per week) of the intervention and waitlist control group. The data used to estimate power come from a previous pilot study, in which the main outcome of interest was the change in frequency of family dinners prepared and eaten at home together (weekly basis) from baseline to post-intervention [42]. Change in frequency of family dinners was used to power the current study because there is strong evidence that it has a downstream effect on the outcome of interest, child BMI [3, 42–44], and there are no previous studies that show a causal effect of family dinners on BMI. Based on these data, assuming 20% attrition [42], with an expected effect size of 0.7071, there will be 80% power to detect a difference in frequency of family dinners of 3 days per week with 30 families per group for a total sample size of 60 families at α = 0.05. Because the sample size in the previous pilot study was small and uncertainty about estimated effect size was large, we used a conservative estimate of effect size (i.e., the lower bound of a 95% confidence interval) for the power calculation.

Data from each of the three cohorts will be pooled and the intervention tested by comparing change (T1-T0) in diet quality, anthropometric measures, and blood pressure of child and caregiver participants in the intervention compared to participants in the waitlist control (hypotheses 1.1 and 2.1). Multiple regression models will be used to determine the association between the difference in the response variables of interest between the intervention and control group, controlling for potential confounders (race/ethnicity, income, cohort, intervention dose), from baseline (T0) to 10-week post-test(T1) and 10-week follow-up (T2). For families in which data will be collected on multiple children, the effect of family will also be controlled by including a random effect for family.

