Sustainability of intervention effects will be tested by pooling intervention group data from each of the three cohorts, comparing change (T2-T1) in diet quality, anthropometric measures, and blood pressure among intervention group participants at the end of the 10-week follow-up period (hypothesis 1.2 and 2.2). Intervention replication will be assessed by pooling waitlist control group data from each of the three cohorts, comparing post-program change in diet quality, anthropometric measures, and blood pressure among waitlist control participants (T2-T1) to intervention participants (T1-T0). Significance will be set at *p* < 0.05.

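### The replication contrast compares two programme periods, so agreement alone cannot show that the programme effect was repeated in waitlist families

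*Protocol article*

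**What the plan says.** In the protocol article, Sample size and data analysis fixes the replication analysis as "comparing post-program change in diet quality, anthropometric measures, and blood pressure among waitlist control participants (T2-T1) to intervention participants (T1-T0", pooled over the three cohorts, with significance at p < 0.05. Study design announces the same aim: "Repeatability of the intervention (replication) will be evaluated by assessing measures on the waitlist control group at T1 and T2".

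The timing is given in the text after Table 1. Families either start the programme at once or choose "to wait for 10-weeks (waitlist control group) after which time they would begin the Simple Suppers program". Allocation is not random: "the personal preference of participating families will determine group membership".

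Waitlist T0 exists. Study design states "Data will be collected on all outcomes via direct measure and questionnaires at baseline (time point 0, T0), 10-week post-test (time point 1, T1"), followed by T2. The main comparison uses it: "the intervention tested by comparing change (T1-T0) in diet quality, anthropometric measures, and blood pressure" between the groups. Neither statement about replication mentions it. The article gives no rule for what result would count as replication.

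**The concern.** A replication analysis should come out differently when the programme works a second time and when it does not work at all. Here the second group's programme period is set against the first group's programme period, with no untreated period on either side. A programme that does nothing in either group is then expected to give the same answer as one that works equally well in both.

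This matters because families choose their own group, and the article itself names the lack of randomisation as a limitation. The waitlist group is the only one observed both untreated and on the programme, so it offers a within-family look at the programme effect. The replication analysis as worded does not use it.

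**Working it through.** **1. The plan's own figure.** The article gives no power for the replication contrast. Its only power statement concerns family dinner frequency in the main comparison: "with an expected effect size of 0.7071, there will be 80% power", "with 30 families per group for a total sample size of 60 families at α = 0.05", allowing 20% attrition.
- 30 per group: 0.7071 × √(30/2) = 2.739, and Φ(2.739 − 1.960) = 0.782 (t test 0.768).
- 24 per group (30 × 0.8): 0.7071 × √(24/2) = 2.449, two-sided power 0.688 (t test 0.669); one-sided 0.790.

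So 80% is roughly met two-sided without attrition, or one-sided with it. Below, 0.7071 serves only as an illustrative standardised effect; the argument does not depend on it.

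**2. Expectation.** Let eI and eW be the programme effects in the intervention and waitlist groups, and g1 and g2 the background changes over the first and second 10 weeks.
- Main effect: E = (T1−T0, intervention) − (T1−T0, waitlist).
- Planned replication contrast: D = (T2−T1, waitlist) − (T1−T0, intervention). Its expectation is (eW + g2) − (eI + g1) = (eW − eI) + (g2 − g1).
- Within-waitlist contrast: W = (T2−T1) − (T1−T0), waitlist only. Its expectation is eW + (g2 − g1).

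Algebraically E + D = W. The informative quantity is already in the data but is not reported. If families who start at once would improve by b more per period on their own, D shifts by −b. W does not, because both of its terms come from the same families.

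**3. Simulation** (20,000 runs; SD of change 1; compound symmetry with correlation 0.5; effect 0.7071 where present; two-sided 5%). Means are for 30 per group; rejection rates are for 30 / 24 per group.

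| Scenario | Mean D | D rejects | Mean W | W rejects |
|---|---|---|---|---|
| Works in both | 0.00 | 5.0% / 5.0% | 0.71 | 58% / 48% |
| Works in neither | 0.00 | 5.1% / 5.1% | 0.00 | 5.0% / 4.7% |
| Intervention group only | −0.71 | 77% / 67% | 0.00 | 4.8% / 5.2% |
| Works in both, trend 0.3 then 0 | −0.30 | 20% / 18% | 0.41 | 24% / 20% |
| Works in neither, trend 0.3 then 0 | −0.30 | 21% / 18% | −0.30 | 15% / 13% |

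D gives the same result for both and neither, with or without unequal trends. W separates the two, but is biased by g2 − g1.

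**4. Precision and shared visits.** With independent visit errors of variance s² and n families per group, var(E) = var(D) = 4s²/n. W is T2 − 2×T1 + T0, so var(W) = (1 + 4 + 1)s²/n = 6s²/n.
- cov(E, D) = (1 − 2)s²/n, so the correlation is −1/4 = −0.25.
- cov(E, W) = (4 − 1)s²/n, so the correlation is 3/√24 = 0.61.
- Power of W: an SD of change of 1 means s² = 0.5, so SE = √(3/30) = 0.316 and 0.7071/0.316 = 2.24, or 58% by t test. With 24, SE = √(3/24) = 0.354, ratio 2.00, 48%.

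**5. Calendar-block model.** Assume three cohorts 10 weeks apart with aligned visits, 8 families per group per cohort, a random family effect, and block terms from all untreated visits. The within-waitlist effect then has variance 3.8 to 7.5 s²/n and correlation 0.26 to 0.55 with E, as the family variance goes from s² to effectively fixed effects. Cohort 3's T2 gets zero weight, because no untreated family shares its block.

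**The case against.** The strongest reply is that efficacy is tested elsewhere, by the T1-T0 comparison with the waitlist group. Replication is a follow-on question: given that effect, do later families change alike? For that question the planned contrast is coherent, and it can fail: if only the intervention group responds, it rejects in 67% to 77% of trials. This stands. A reader might infer that the contrast can neither support nor count against the programme; that is too strong.

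The reply does not rescue agreement as evidence. The step from agreement to replication borrows everything from the main effect, which rests on self-chosen groups. Agreement is also loose: with 30 per group the SE of D is √(2/30) = 0.258, so even D = 0 leaves a difference in effects of about 1.96 × 0.258 = 0.51 SD open.

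The Study design sentence could be read as a plain waitlist change from T1 to T2. That does carry the effect (96% against 5% rejection with 30 per group and no trend), but it has no untreated comparator: with no effect and an assumed trend of 0.3 SD per period it rejects 35% of the time. The analysis section also specifies the between-group contrast instead.

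Two further inferences fail. Waitlist T0 is not discarded from the trial; it is absent only from the replication analysis. Nor does reuse of waitlist T1 make a false-positive main result look replicated on the planned contrast: the correlation is −0.25, so a chance-high main effect pushes D away from agreement. A positive correlation (1/√8 = 0.35) belongs to the waitlist T2-T1 change tested against zero, which is a different test.

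Finally, replication is not among the numbered hypotheses or the main outcomes, and the article condenses a fuller plan. Both limit the weight of the point, but the contrast itself is stated explicitly.

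**Conclusion.** The point holds in limited form. An effect common to both groups cancels from the planned contrast whatever the trends. That its expectation is exactly zero also needs equal background trends in comparable groups. The contrast can show that the two programme-period changes differ. By itself it cannot show that the programme effect was replicated in waitlist families. The main comparison is unaffected.

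The rejection rates rest on the assumed effect of 0.7071 SD and compound symmetry; the cancellation does not.

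A reader might take the within-family contrast to be free of self-selection, or to be independent confirmation. It is neither. It removes fixed differences between families, and steady differences in their trends, but not calendar, seasonal or repeat-measurement change. It also shares waitlist T0 and T1 with the main effect (correlation about 0.61).

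**What to change.** Keep the planned contrast, described as a check that the two groups' programme-period changes are similar. Add as the replication estimate the programme effect within waitlist families: their T2-T1 change minus their own T1-T0 change, with a 95% CI, reported beside the main between-group effect. Claim replication only if that interval excludes zero in the direction of the main effect. A mixed model with calendar-block terms from untreated visits can serve as a sensitivity analysis.

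The cost is analysis wording only; every visit is already planned. The plan should state the downsides:
- Power is about 48% to 58% at an effect of 0.7071, so failure to exclude zero is weak evidence against replication.
- The estimate is correlated with the main effect.
- It remains exposed to calendar or seasonal change.
- In the calendar-block model, cohort 3's T2 contributes nothing.

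Comparing T2 with the plain average of T0 and T1 is no way round this. It is more precise only without a trend; a linear trend of g per period biases it by 1.5g, whereas T2-T1 minus T1-T0 cancels such a trend.

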## Discussion

We may encounter challenges engaging and developing trust with the target population, an issue that is common to intervention research with economically disadvantaged families [45–47]. However, this study was designed to minimize this potential barrier by implementing the intervention at a local faith-based community center, which has established relationships with the target population. In addition, this study will engage current staff from the faith-based community centers to serve as educators in delivering the intervention. Grounding the caregiver component in Adult Learning Theory will further enhance our abilities to engage with families, as this approach is designed to present new information in a non-threatening, approachable way.

Another limitation is the lack of randomization study design. Randomization was not appropriate for this study because preserving sample size and developing trust with the site/participating families was paramount [47–49]. We will overcome this limitation by assessing potential between- group differences at baseline and, if identified, will be controlled for in the analyses.

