A key affective variable - caregiver self-efficacy for healthy dietary practices related to family meals - will be assessed using an existing 12-item, 10-point scalar (0 = not at all confident; 10 = extremely confident) questionnaire [37]. The caregiver self-efficacy questionnaire, which will be completed by caregiver participants at each data collection point, has demonstrated high internal consistency (α = 0.88) among a sample of caregivers of 4–6 year old children. Tests of internal consistency will be run on all of the aforementioned questionnaires. Caregivers will also complete a brief food security questionnaire at each data collection point (6-item Short Form of the USDA Home Food Security Survey) [38] and a demographics questionnaire to assess key participant characteristics (age, race/ethnicity, education, employment, income) at baseline.

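### Families choose their own group, yet covariates beyond a short fixed list enter the model only if a baseline difference is identified, and this is said to overcome the lack of randomisation

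*Protocol article*

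**What the plan says.** All references are to the Protocol article.

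- **Allocation** (Methods, Study design, after Table 1): "Following baseline data collection, families will decide whether to enroll" in the coming session or wait ten weeks, and "the personal preference of participating families will determine group membership". The reasons given are scheduling, wishing to attend with families they know, and building trust.
- **Fixed covariates** (Sample size and data analysis): the regression models are described as "controlling for potential confounders (race/ethnicity, income, cohort, intervention dose"), with a random effect for family where several children are measured.
- **Response** (same section): the main test is described as "comparing change (T1-T0) in diet quality, anthropometric measures, and blood pressure". The baseline value of the outcome is not named as a covariate.
- **Further covariates** (Discussion): on non-randomisation, "We will overcome this limitation by assessing potential" between-group "differences at baseline and, if identified, will be controlled for in the analyses".
- **Collected but not on the fixed list** (Personal determinants; Family meals): age, education and employment from "demographics questionnaire to assess key participant characteristics (age, race/ethnicity, education, employment, income) at baseline", food security at each data collection point, and the family-meal items, which are also measured at baseline.

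**The concern.** Families who start at once may differ from those who wait in motivation, free evenings and existing meal habits. These are plausible causes of change in diet and meal frequency, so confounding is the main threat to every T1-T0 comparison.

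The stated defence has three weaknesses.

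1. **The trigger.** A variable confounds because of its relation to group choice and to outcome. Whether a difference shows up in a sample of 60 families is a separate matter. A trigger based on the observed difference will pass over real imbalances, and the final model is then chosen after the data are seen. The reported p-values and intervals do not reflect that choice.
2. **The fixed list.** Intervention dose is received after allocation, so it cannot be a baseline confounder. Three listed covariates remain to deal with self-selection, although several other relevant baseline variables are collected.
3. **The claim.** Adjustment for measured variables cannot remove unmeasured motivation or scheduling preference, so saying that the limitation will be overcome promises too much.

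This is more than detail left to an analysis plan: the article itself states the list, the rule and the claim.

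**Working it through.** **Inputs from the article:** effect size 0.7071, 30 families per group, 20% attrition (30 x 0.8 = 24 completers per group), alpha 0.05 with sidedness not stated, power 80%.

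**Assumptions, not in the article:** an identified difference means a two-sided 5% t-test; selection acts through the baseline outcome; baseline-to-T1 correlation r is 0.5 or 0.7; equal variances; no true effect.

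**Step 1: the plan's own figure.** Noncentrality = d x sqrt(n/2); normal approximation.
- 24 per group: 0.7071 x sqrt(12) = 2.449. Two-sided power is Phi(2.449 - 1.960) = 0.69; one-sided power is Phi(2.449 - 1.645) = 0.79.
- 30 per group: 0.7071 x sqrt(15) = 2.739. Two-sided power is Phi(2.739 - 1.960) = 0.78.

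So 80% is approximately reproduced as one-sided with attrition or two-sided without it. Nothing below depends on which was meant; this step only fixes the group sizes of 24 and 30.

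**Step 2: how often the screen would find a real imbalance.** Same noncentrality, noncentral t with 2n - 2 degrees of freedom, two-sided 5%.

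| True imbalance (SD) | 30 per group | 24 per group |
|---|---|---|
| 0.2 | 12% | 10% |
| 0.3 | 21% | 17% |
| 0.5 | 48% | 40% |
| 0.7 | 76% | 66% |

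Imbalances up to 0.5 SD would be missed more often than found.

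**Step 3: bias if the baseline outcome is never adjusted for.** Let the intervention group start delta = 0.5 SD higher. The expected difference in change is -(1 - r) x delta.
- r = 0.5: -0.5 x 0.5 = -0.25 SD.
- r = 0.7: -0.3 x 0.5 = -0.15 SD.

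The sign reverses if the intervention group starts lower. At r = 0.5 the SD of change is sqrt(2 x (1 - 0.5)) = 1, so the noncentrality at 24 per group is 0.25 x sqrt(12) = 0.87 and the two-sided false-positive rate is about 14%.

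**Step 4: bias under the stated rule.** In a simulation with no true effect and a 0.5 SD imbalance, the baseline outcome was added to the change model only when its baseline test was significant. Ranges cover 24 and 30 per group.

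| Analysis | r = 0.5: bias (SD), false positives | r = 0.7: bias (SD), false positives |
|---|---|---|
| Never adjust | 0.25, about 14-16% | 0.15, about 10-12% |
| Adjust only if significant | 0.08-0.10, about 6% | 0.05-0.06, about 6% |
| Always adjust | about 0, 5% | about 0, 5% |

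At r = 0.5, in the samples where the screen misses the imbalance, bias is about 0.15-0.16 SD and false positives are about 7%. It stays below 0.25 SD because the missed samples are those with smaller observed differences.

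**Step 5: relative size.** At r = 0.5, 0.08/0.7071 = 11% and 0.10/0.7071 = 14% of the planned effect size. These figures concern one covariate; other unlisted predictors could add to them or offset them.

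**The case against.** Several counter-arguments have force.

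- **No significance test is stated.** Correct: the Discussion names no test or threshold. The detection rates in step 2 are conditional on an assumption. If some other criterion is meant, the rule is undefined, which still leaves the adjustment set open.
- **Some covariates are always included.** Correct: race/ethnicity, income and cohort enter whatever the balance. A reader might infer that the plan adjusts solely for observed differences; the analysis section does not support that. The point concerns variables beyond the fixed list.
- **A reader might infer a bias of 0.25 SD and a false-positive rate of 14%.** Those figures apply only if the baseline outcome is never adjusted for. The stated plan would adjust for it when a difference is found, which brings false positives close to nominal.
- **A change score already uses the baseline value.** This stands. If stable differences between self-selected groups would have persisted (parallel trends), the unadjusted change score can be the unbiased estimator, and conditioning on baseline can introduce bias. The article does not show which mechanism operates, so leaving out the baseline outcome cannot simply be called an error. What is missing is any acknowledgement that the two analyses rest on different assumptions.
- **A condensed article need not list every covariate.** This also stands. An incomplete list alone would be no finding; the data-driven trigger and the claim attached to it are stated outright.
- **The limitation is openly admitted.** It is, but the article then says that it will be overcome.

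**Conclusion.** The point holds at moderate size. The trigger is not a sound way to choose confounders in a trial with self-selected groups, it leaves the model open until the data are seen, and the claim to overcome non-randomisation cannot be met.

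Under the stated assumptions (5% screen, selection through the baseline outcome, 0.5 SD imbalance, r from 0.5 to 0.7), the remaining average bias is about 0.05 to 0.10 SD and the false-positive rate about 6%, against about 0 and 5% if the baseline outcome is always included. Under parallel trends this comparison would not favour baseline adjustment. Confounding by unmeasured preference is not quantified here and remains under any of these analyses.

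**What to change.** 1. Drop the conditional trigger. Prespecify on subject-matter grounds a short set from variables already collected, for example income, race/ethnicity, cohort, education, food security and baseline family-dinner frequency. Alternatively, use a single propensity score built from that set.
2. Do not count intervention dose as a confounder.
3. Report the change-score model and the model adjusted for the baseline outcome side by side, stating the assumption behind each. For the dinner-frequency outcome, baseline dinner frequency is the baseline outcome, so it belongs only in the second model.
4. In the Discussion, say that adjustment will reduce confounding, and that unmeasured motivation and scheduling preference remain.

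**Cost:** wording only; no new data. The example set uses at least seven degrees of freedom (two for three cohorts, one for each of the other five, more if they are multi-category) in about 48 completing families. That is a reason to keep the set short or to use the propensity score.
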